## Abstract

**Purpose:**

The SALUS study aims to improve the healthcare situation for glaucoma patients in Germany. In order to detect diurnal intraocular pressure (IOP) fluctuations, inpatient monitoring of IOP in an eye hospital for a minimum of 24 h is the current standard. SALUS assesses the benefits of a new form of outpatient care, where IOP can be measured by the patients themselves at home using a self-tonometer. This approach should promote the patient’s health competence and empowerment within the healthcare system while reducing treatment costs.

**Methods:**

The SALUS study is a randomized controlled, open non-inferiority trial, alongside an economic analysis, determining whether outpatient monitoring of IOP with self-tonometry is at least as effective as current standard care and would reduce treatment costs. Participants (*n* = 1980) will be recruited by local ophthalmologists in the area of Westphalia-Lippe, Germany, and randomized to receive 7-day outpatient or 24-h inpatient monitoring. Participants in both study arms will also receive 24-h blood pressure monitoring. Furthermore, patient data from both study groups will be collected in an electronic case file (ECF), accessible to practitioners, hospitals, and the study participants. The primary endpoint is the percentage of patients with IOP peaks, defined as levels 30% above the patient-specific target pressure. Data will also be collected during initial and final examinations, and at 3, 6, and 9 months after the initial examination.

**Results:**

The study implementation and trial management are represented below.

**Conclusion:**

SALUS is a pioneering prospective clinical trial focused on the care of glaucoma patients in Germany. If SALUS is successful, it could improve the healthcare situation and health literacy of the patients through the introduction of various telemedical components. Furthermore, the approach would almost certainly reduce the treatment costs of glaucoma care.

**Trial registration:**

*ClinicalTrials.gov ID:* NCT04698876, *registration date:* 11/25/2020.

*DRKS-ID:* DRKS00023676, *registration date:* 11/26/2020.

[figure not shown]

## Introduction

Glaucoma is one of the most common chronic eye diseases with almost one million affected individuals in Germany and rising tendency, as the risk of glaucoma increases with age [1]. The disease results in an irreversible loss of optic nerve fibers with associated progressive visual field damage, leading to complete blindness if left untreated or poorly treated [1]. Currently, glaucoma is still one of the leading causes of blindness in Western industrialized countries [1]. It is hypothesized that an elevated intraocular pressure (IOP) and a lack of blood supply to the optic nerve head both contribute to the progressive loss of retinal ganglion cells. Though sophisticated imaging techniques, like optical coherence tomography (OCT) of the optic nerve head with assessment of the retinal nerve fiber layer (RNFL) thickness and of Bruch’s membrane opening minimum rim width (BMO-MRW) and, more recently, OCT angiography (OCTA), are available to diagnose and assess glaucoma progression, the IOP is still the only direct control parameter of therapy response.

Studies show that lowering the IOP reduces the rate of glaucoma progression and decreases the frequency of a progression from ocular hypertension to glaucoma [1–3] Typically, IOP controls in glaucoma patients are performed three to four times per year. However, the IOP as a control parameter can be subject to large fluctuations with pressure peaks during the day, and such pressure fluctuations are especially common in glaucomatous eyes [4, 5]. Prior to the start or adjustment of therapy, measurement of IOP in hospitals at 4-h intervals over several days (minimum 24 h) can be helpful, especially in the case of disease progression despite normal IOP measured on an outpatient basis or in the case of unclear optic nerve disorders. Goldmann applanation tonometry (GAT) and rebound tonometry are commonly used. The measurements are usually performed by doctors or other medically qualified personnel. Several studies have confirmed the importance of 24-h IOP monitoring, demonstrating that more than half of all glaucoma patients have their peak IOP outside conventional working hours [6, 7]. A study comparing 24-h inpatient IOP measurements with those taken during normal working hours showed that implementing 24-h IOP monitoring led to a change in clinical management in 79.3% of patients [8].

The new, commercially available IcareHOME® self-tonometer enables patients to take their own IOP measurements. This could reduce the need for inpatient stays. Evaluation of data from these devices by the attending ophthalmologist nevertheless ensures professional support of the patients and enables therapy planning to be based on the data collected. However, self-tonometry has not yet been incorporated into standard care in Germany.

Termühlen et al. demonstrated comparable IOP values in GAT and self-tonometry. In addition, the taking of measurements by the physician and by the patient were found to be comparable [9]. Even though some patients were more than 75 years old, their rating of the self-tonometer in the categories usability, feeling of safety, and comfort lay between “satisfied” and “very satisfied.” The time taken for an average measurement was between 45 s (younger patients) and 88 s (older patients) for both eyes [10].

Pilot projects for telemedical home monitoring of IOP have been carried out at the University Eye Hospital Greifswald with positive effects on care [11, 12]. Dietlein et al. analyzed the data of 130 glaucoma patients and concluded that an increase in understanding of the disease, better motivation to increase compliance, and more practical involvement of patients are necessary [13, 14]. Lämmer et al. concluded in their study that the compliance generated by the close doctor-patient relationship within telematically assisted self-tonometry is a positive prognostic factor for glaucoma [11].

Based on these findings, the overall objective of the SALUS study, standing for “Self Tonometry and Transfer of Glaucoma Patients’ Data for Improving the Supply Situation,” is to determine the effectiveness, acceptability, and reliability of outpatient monitoring of IOP using an IcareHOME® self-tonometer, compared to the existing standard procedure in Germany. Since self-tonometry does not require admission to hospital, this new approach could potentially reduce costs and improve the quality of care for glaucoma patients.

More specifically, the SALUS study aims to demonstrate that self-tonometry is non-inferior to the established 24-h inpatient IOP measurements for monitoring and treating glaucoma. The primary hypothesis in this non-inferiority trial is that the percentage of patients in whom pressure peaks could be detected during the pressure profile would not differ significantly between the intervention group (IG = outpatient self-tonometry) and the control group (CG = inpatient measurement every 3 h over the course of 24 h). In this study, a pressure peak was defined as a level 30% above the patient-specific target pressure which will be set by the treating ophthalmologists. The health economic hypothesis tests whether the use of self-tonometers reduces costs from a healthcare provider perspective compared to current standard care.

## Materials and methods

### Study design

The SALUS study is a multicenter, two-arm parallel group, open non-inferiority, randomized controlled trial with an economic analysis alongside.

This non-inferiority design was chosen to establish that outpatient monitoring of IOP with self-tonometry is not less effective than standard care with hospitalized monitoring of IOP. The trial will be conducted in hospitals and patients’ homes in the district of Westphalia-Lippe, Germany. Each participant will be followed for 12 months from the start of the trial, with regular follow-up every 3 months by local ophthalmologists (see Fig. 1).

**Fig. 1 Fig1:**
[figure not shown]
Study flow chart

### Intervention

The main part of the intervention is outpatient monitoring of IOP using a self-tonometer. The glaucoma patients who qualify to participate in the study will be briefed by the local ophthalmologist about the study design as well as the benefits and risks and asked to sign an informed consent form. After randomization, they will be contacted by the Department of Ophthalmology of the University of Muenster Medical Center to arrange an appointment at one of the participating eye hospitals for an initial examination.

The initial examination includes IOP measurement to investigate the pathological pressure peaks, a 30° visual field examination, an OCT of the optic nerve head, a Heidelberg retina tomography (HRT) (if available), and a questionnaire about health-related quality of life. Subsequent to the initial examination, patients will be instructed by the clinical staff in the functioning and handling of the IcareHOME® self-tonometer and 24-h blood pressure measuring device. The patients of the IG will then receive the devices and perform self-tonometry over the course of seven days. They will also undergo initial blood pressure monitoring for 24 h, starting at the end of the training. The IOP and blood pressure values measured will be evaluated by the local ophthalmologists, who can adjust the patient’s therapy on the basis of the results. Thereafter, check-ups will be carried out every 3 months by the local ophthalmologists. The final examination will be performed 12 months after the initial examination at the same participating eye hospital and will replicate the initial one but end with a final interview between the doctor and patient.

All measured values, the medical history, and the imaging performed will be transferred by the local ophthalmologists or hospitals to an electronic case file (ECF), a cloud-based system for the management of the patient’s primary data. The ECF can also be used to raise queries with a glaucoma specialist and senior resident from the University of Muenster Medical Center. IG participants will also have access to the ECF and be able to view all measurement data. The participants will gain a comprehensive insight into their disease progression for the first time and will also become more involved and informed about treatment options.

### Study population, sampling strategy, and eligibility criteria

All patients with confirmed or suspected glaucoma who require inpatient day and night IOP monitoring within the state of Westphalia-Lippe will be invited to participate in this study. Confirmed or suspected glaucoma will be classified according to the international ICD-10 classification (see Table 1). Patients eligible to participate in SALUS will be identified by their local ophthalmologists during initial consultations for glaucoma or routine check-ups. Fulfilment of inclusion or exclusion criteria (Table 1) and recruitment will be established by the ophthalmologists based on their clinical experience. Eligible patients, willing to participate, will receive an information sheet explaining details of the study and the terms intervention and randomization and be asked to provide written informed consent before randomization.

**Table 1 Tab1:** Inclusion and exclusion criteria

Inclusion criteria	Exclusion criteria
I. 18 years of age or older	I. Younger than 18 years of age
II. Requiring inpatient day and night IOP monitoring	II. Patients outside of the usual catchment area of the participating hospitals
III. Statutory health insurance	III. Concomitant psychiatric or neurological diseases or other conditions limiting the ability to perform self-tonometry independently
IV. Confirmed or suspected glaucoma with pressure variations and peaks, failure to achieve intraocular target pressure or progression of glaucoma (ICD-10 H40.0 Glaucoma suspect, H40.1 Primary open-angle glaucoma, H40.2 Primary angle-closure glaucoma and H42.- Glaucoma in diseases classified elsewhere)	
V. Willingness to be admitted to one of the participating hospitals as an inpatient	IV. Strong barriers to communication that would not allow informed consent or understanding of patient information
VI. Sufficient knowledge of German	
VII. Signed and dated informed consent for study participation and data transfer	V. Unclear legal capacity to agree to participate in the study
VIII. Legal capacity to agree to participate in the study	

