### Secondary endpoints

#### Clinical endpoints

Visual field indices such as visual field index (VFI), mean deviation (MD), and pattern standard deviation (PSD) will be determined using standard automated perimetry. These values will be measured on initial and final examination in hospitals and after 9 months during the follow-up visit at the local ophthalmology practice. These measurements will be used to determine the extent of visual field loss due to suspected or confirmed glaucoma. Furthermore, the values will be used to calculate visual field damage and classify stages of glaucoma [20, 21].

RNFL thickness, rim volume, and rim area will be needed to map short- and medium-term results of glaucoma diagnosis and progression within the project time-frame [22]. Those surrogates will be determined with OCT (RNFL thickness) and HRT (rim volume and area), if available, during initial and final examination in participating hospitals.

IOP will be measured on all examinations in participating hospitals and at the local ophthalmology practice. Since low ocular perfusion pressure and low blood pressure are associated with an increased risk of glaucoma, vascular factors can be of importance for further glaucoma treatment planning [23]. Measurement of blood pressure will be performed parallel to IOP monitoring during inpatient stay or at home for 24 h, every 15 min during day between 6 a.m. and 10 p.m. and every 30 min at night between 20 p.m. and 6 a.m.

Health-related quality of life will be evaluated using the EQ-5D-5L questionnaire, a generic multidimensional instrument implemented by the EuroQol Group [24, 25]. The EQ-5D is frequently used to analyze quality of life in ophthalmic diseases such as glaucoma, and glaucoma and disease progression with visual damage are known to influence health-related quality of life [26–29].

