### Sample size

The sample size was determined using the license-free software “R” (R v. 3.6.3, Rstudio v. 1.2.5042). The estimation of sample size and power analysis is based on the primary endpoint “exceeding patient-specific target pressure”. As null hypothesis, it is assumed that the proportion of pressure peaks in IG is smaller than the proportion in CG (i.e., non-inferiority).

Based on clinical experience, a margin of 20% is assumed for detection of IOP fluctuations and peak values in both groups. A non-inferiority margin of *δ* = 0.05 is acceptable, meaning the proportion of pressure peaks in self-tonometry should fall below the proportion in 24 h IOP by more than 5% to be taken as a statistically significant difference [34, 35]. With regard to the probability of type I and II errors, significance levels will be set at *α* = 0.05 and *β* = 0.2, respectively, i.e., a power of (1 − *β*) = 0.8. This results in a total of 1584 patients (792 per group). After adjusting for a drop-out rate of 20%, a final sample size of 1980 patients (990 per group) will be required for this trial (see Fig. 2).

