## Results

### Selection and recruitment of local ophthalmologists and patients

Since local ophthalmologists will assess the need for the intervention, they will decide which patients to include in the study. The ophthalmologist will inform all patients who would receive inpatient monitoring of IOP as standard care about the SALUS study. There will be no selection based on severity of illness or criteria other than the inclusion and exclusion criteria of the study (Table 1).

In general, every ophthalmologist in Westphalia-Lippe will have the opportunity to participate in the project. The recruitment of ophthalmologists appears to be particularly effective with a good cost–benefit ratio. Those with a high number of glaucoma patients are preferentially recruited, not least because such practices are likely to enroll the most patients in the study. The work involved should be communicated to the ophthalmologists in an easily understandable and concise manner, while any further effort on their part should be kept to a minimum. The ophthalmologist should be able to access information at self-selected times. The trial will be brought to the attention of the ophthalmologists mainly via e-mails, letters, information events, website, and articles. Participating ophthalmologists will get a detailed study folder with all relevant documents and a guideline for briefing the glaucoma patients to make the procedures standardized. They can also attend optional training sessions.

Patients will be informed by project flyers or addressed directly by the physicians. An information hotline will be available on weekdays for all interested parties. High drop-out numbers are not expected for patients assigned to the CG, as they will receive services that are current standard care. There is just one additional appointment at the end of the study period, which is the final examination in the eye hospital. It is assumed that the patients will take advantage of this, on account of the intensive care and additional review of their disease and medication, which could help to avoid further complications and the risk of blindness.

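### Patients already above 1.3 × target at entry will tend to score as detected in both arms; adjust for entry pressure and add a supportive analysis without them

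*Protocol article*

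**What the plan says.** Inclusion criterion IV (Table 1) admits patients with "Confirmed or suspected glaucoma with pressure variations and peaks, failure to achieve intraocular target pressure or progression of glaucoma". It sets no upper limit on entry pressure relative to target, and the section on recruitment adds: "There will be no selection based on severity of illness or criteria other than the inclusion and exclusion criteria of the study".

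The Introduction defines the event: "a pressure peak was defined as a level 30% above the patient-specific target pressure which will be set by the treating ophthalmologists". No rise over the patient's own level is required. The article does not say when the target is fixed.

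The hypothesis concerns "the percentage of patients in whom pressure peaks could be detected during the pressure profile would not differ significantly between the intervention group" and the control group. Under Sample size, "a margin of 20% is assumed for detection of IOP fluctuations and peak values in both groups", with a margin of 0.05 on the proportion of all patients.

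On available data, "IOP will be measured on all examinations in participating hospitals and at the local ophthalmology practice", and Table 2 schedules a pressure measurement at T−1, enrolment by the local ophthalmologist. The web form completed before randomization is described as holding master data and eligibility criteria; neither the pressure nor the target is listed. Statistical analyses foresees an unspecified regression model for the primary endpoint, and subgroup analyses with time, age and gender as examples.

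**The concern.** Entry and outcome are partly the same thing. A patient may be enrolled because the target is missed, and is then scored positive for exceeding a multiple of the target. With a target of 15 mmHg the threshold is 1.3 × 15 = 19.5 mmHg, so a flat profile at 20 mmHg counts as a detected peak although it contains no fluctuation.

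The Introduction says that pressure profiles are especially helpful in "disease progression despite normal IOP measured on an outpatient basis", that is, where office readings do not reveal the problem. Patients whose office reading already lies above the threshold cannot show much about that ability. They add similar numbers of positives to both arms. In a superiority trial this dilution would be conservative; in a non-inferiority trial it favours the conclusion sought. Randomization does not cure it, because the difficulty is loss of assay sensitivity and not imbalance.

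At stake is whether a finding of non-inferiority can be read as saying that self-tonometry finds the peaks that only a profile can reveal.

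**Working it through.** **Inputs.** From Sample size: rate 0.20 in both arms, margin 0.05, α = 0.05, power 0.80, 792 evaluable per arm, 20% drop-out, 1980 in total. Assumed, because the article does not give it: s, the share of all patients above 1.3 × target at T−1, here 0 to 10%.

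**The plan's own figure.** n per arm = (1.645 + 0.842)² × 2 × 0.20 × 0.80 / 0.05² ≈ 791.4, so 792 and 1584 in total; 1584 / 0.8 = 1980. It reproduces with a one-sided 5% level (one-sided 2.5% would give 1005 per arm). The sample-size arithmetic is not at fault.

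**Dilution with the overall rate held at 20%.** Write the control rate as 0.20 = s + h, where the share s is positive in both arms and h is positive only through the profile. If the intervention arm misses a fraction m of h, the overall difference is −m × h. The loss that sits exactly at the margin is 0.05 / h. The chance of declaring non-inferiority is Φ[(0.05 − m × h)/SE − 1.645], with SE = √[(pC(1 − pC) + pI(1 − pI))/792], pC = 0.20 and pI = 0.20 − m × h. For m = 25%:

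| s | h | loss at the margin | pI | SE | chance of passing |
|---|---|---|---|---|---|
| 0 | 0.20 | 25% | 0.1500 | 0.0191 | 5% |
| 5% | 0.15 | 33% | 0.1625 | 0.0193 | 16% |
| 10% | 0.10 | 50% | 0.1750 | 0.0196 | 36% |

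**Dilution with the rate among the remaining patients held at 20%.** The overall rate is then s + 0.20(1 − s), and the margin among the remaining patients becomes 0.05/(1 − s). At s = 10% and 20% the overall rate is 28% and 36%, and the margin 5.6 and 6.25 points. A true 5-point deficit among the remaining patients passes with probability 8% and 11%. Power at true equality falls from 80% to 72% and 67%.

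**Precision recovered by adjustment.** Let f be the probability that a patient above the threshold at entry scores positive. Among the others the rate is q = (0.20 − s × f)/(1 − s), and the variance within entry strata is V = s × f(1 − f) + (1 − s) × q(1 − q), against 0.160 unadjusted. Power at equality is Φ[0.05/√(2V/792) − 1.645].

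| s | f | V | power |
|---|---|---|---|
| 5% | 70% | 0.147 | 83% |
| 5% | 85% | 0.138 | 85% |
| 5% | 100% | 0.126 | 88% |
| 10% | 70% | 0.132 | 86% |
| 10% | 85% | 0.113 | 91% |
| 10% | 100% | 0.089 | about 95% |

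Adjustment sharpens the overall difference but leaves its meaning unchanged. The dilution itself becomes visible only in the analysis of patients below the threshold at entry.

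**The case against.** **Population.** The trial asks whether home monitoring can replace admission for everyone who would be admitted, by intention to treat. Patients above target belong to that group, and the Introduction says that profiles help especially, not only, where office pressure is normal. This stands: the primary population should remain as planned, and the set below the threshold should be supportive.

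**Positive in both arms is an assumption.** Missing the target is not the same as exceeding it by 30%. Pressure may change between T−1 and the profile, and a patient with high pressure may still be missed at home through non-use or failed measurement. This also stands, and makes the dilution figures upper-end ones.

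**Size.** A reader might go further and infer that self-tonometry could miss every profile-only peak and still pass. That follows arithmetically at s = 15% (0.05/0.05 = 100%), but it requires three quarters of the planned positives to be above the threshold at an office visit, and nothing in the article supports this.

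**Patients modestly above target.** A reader might also infer that they too add equal positives to both arms through measurement noise alone. The schedule does not support this: six times daily for 7 days gives the intervention arm 42 occasions, against at least 24 h in the control arm. Unequal observation is a separate matter, which the adjustment proposed here does not address.

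**Analysis-plan territory.** The regression model and subgroups are described openly enough to include entry pressure, and a statistical analysis plan may do so. The point is therefore not that the article forbids it. It is that the article pairs this entry criterion with this endpoint, and that the adjustment needs a target recorded before allocation, which the article does not secure.

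**Conclusion.** The point holds as a recommendation on analysis and data capture, not as an error that invalidates the design. Criterion IV and the peak definition overlap, and patients above the threshold at T−1 will tend to dilute the comparison towards non-inferiority.

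For an assumed s of 5% to 10% at the planned rate, the margin tolerates losing 33% to 50% of the remaining peaks instead of 25%, and a true 25% loss passes with probability 16% to 36% instead of 5%. This rests on s, which is unknown, on entry pressure persisting to the profile, and on near-certain detection of these patients in both arms. Dilution does not always help the sponsor: if these patients raise the overall rate above 20%, power at equality falls.

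The article does not support the reading that all patients who miss their target are foregone positives, nor that the trial's sole purpose is to find peaks hidden from office readings. Patients enrolled for progression at normal office pressure remain fully informative.

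**What to change.** 1. Record each patient's target pressure together with the T−1 pressure before randomization, for example on the existing web form. Allocation is open, so a target set later could depend on the arm; for the same reason use T−1 and not T0, which follows randomization. Adjust the primary risk difference for T−1 pressure relative to target, for example as a standardised risk difference, and keep the 5-point margin. Power at equality rises from 80% to about 83–91% for s = 5–10% if 70–85% of the patients above the threshold score positive, and at most to 88–95%.

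2. Pre-specify a supportive analysis in patients with T−1 pressure below 1.3 × target. Report the risk difference and the ratio of the two arms' rates with intervals, and word the conclusion in the light of it. It should not be a gate: requiring the ratio's one-sided 95% bound to clear the plan's implied 0.15/0.20 = 0.75 would succeed under true equality in only 78% (s = 5%) or 61% (s = 10%) of trials.

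Cost: two fields secured before allocation and some analysis-plan wording; no extra patients or visits. The downside is one further analysis with a wider interval, which may be less favourable than the headline result.
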